## Abstract

**Background:**

Postoperative rehabilitation following total knee arthroplasty (TKA) varies worldwide. In Finland, patients receive guidance on safe walking and home exercises from a physiotherapist both before and after TKA. These are performed independently after surgery. However, a sedentary lifestyle is rather common among patients who have undergone TKA, with pain often limiting postoperative walking, training, and activities of daily living.

**Objective:**

This randomized controlled trial aimed to investigate the effectiveness of anti-gravity exercise, precisely the AlterG anti-gravity treadmill, on postoperative rehabilitation following TKA and to obtain new knowledge on this form of rehabilitation to better use it in the future.

**Methods:**

This randomized controlled trial study divided the patients into two groups: the intervention group and the control group. The follow-up period was 12 months. Research data were collected through questionnaires and functional tests. All patients in both groups responded to the questionnaires and participated in functional tests before surgery as well as 4 and 12 months after surgery. Patients in the intervention group exercised on the AlterG treadmill 10 times after the surgery. All the patients in this study performed the exercises as instructed when they were in the hospital. The primary outcomes were perceived pain, walking ability, and quality of life.

**Results:**

The data collection process began in 2018 and concluded in 2022, intending to obtain valuable information regarding the effect of AlterG training after TKA and determine whether it, along with traditional exercises, could be an effective form of rehabilitation that can be performed at home. We hypothesized that AlterG training would lead to faster rehabilitation, better walking quality, improved quality of life, improved physical activity, and improved overall functioning. The results of this study will be analyzed in 2025 and 2026.

**Conclusions:**

This study provides information on how AlterG training can be used in rehabilitation after TKA, further enhancing the rehabilitation program for patients undergoing TKA in general.

**Trial Registration:**

ClinicalTrials.gov NCT03904030; https://clinicaltrials.gov/study/NCT03904030

**International Registered Report Identifier (IRRID):**

DERR1-10.2196/59935

## Introduction

### Overview

Pre- and postoperative rehabilitation for total knee arthroplasty (TKA) varies worldwide [1-3]. There are guidelines for postoperative physiotherapy after TKA [4], and physiotherapy guidance for self-directed home exercises is recommended [5]. In Finland, the current care guidelines provide guidance for pre- and postoperative rehabilitation [6], but the practices associated with the rehabilitation vary among different hospitals. Previous studies have shown that both inpatient and home-based rehabilitation are effective after TKA [7] and that resistance training in water is a feasible mode of rehabilitation with a wide range of positive effects on patients undergoing TKA [8]. Reportedly, a sedentary lifestyle is rather common among patients who have undergone TKA, with pain or discomfort while standing being the greatest barrier to increasing physical activity [9]. Pain limits postoperative walking training and activities of daily living [10].

Anti-gravity exercises could help address these challenges. They enable a more objective analysis of walking, showing the entire picture of a patient’s walking problems. AlterG (AlterG, Inc., Fremont, CA), a patented compressed air technology (NASA differential air pressure technology), can be used to lighten the user’s body weight and the load of gravity with 1% accuracy, thereby enabling a less painful walking exercise compared to normal land-based training [11]. While there is limited research on the effects of AlterG training, randomized controlled trials (RCTs) with small sample sizes have been reported, particularly among patients with neurological disorders, such as cerebral palsy [12] and stroke [13,14]. These studies demonstrated that AlterG training positively affected walking speed and dynamic balance and reduced the risk of falls [12-14]. Similar results were reported in studies investigating the effects of AlterG training in rehabilitation after lower limb fractures [15,16]. Precisely, it was found that AlterG training increased muscle strength in the hip area [15] and enabled better walking [16].

A pilot study on AlterG training after TKA revealed that it increased functional ability and is thus overall a safe, useful, and effective rehabilitation method after TKA [17]. Although previous researchers [17] concluded that while functional outcomes improved over time with the use of anti-gravity gait training, further studies with a larger sample size are required to define the role of this device as an alternative or adjunct to established rehabilitation protocols [17]. Furthermore, AlterG training in the acute phase of postoperative knee rehabilitation after knee surgeries, such as TKA and anterior cruciate ligament reconstruction, demonstrated a positive effect on balance in patients experiencing increased pain in weight-bearing postures [18]. AlterG training also decreased pain, enhanced joint function, improved quality of life (QoL), and maintained thigh muscle strength gains in patients with knee osteoarthritis [19]. However, as previously mentioned, not much research has been conducted on postoperative rehabilitation including AlterG training after TKA [17,18], thereby warranting further studies in the future to obtain more knowledge regarding its effects on walking and functional capacity.

### Aims and Objectives

The exposures under investigation were the effects of anti-gravity treadmill training in postoperative rehabilitation following TKA and the added value it offered compared to traditional exercise. We hypothesized that AlterG training after hospitalization leads to faster rehabilitation, better walking quality, improved QoL, improved physical activity, and enhanced balance management compared to traditional rehabilitation methods with instructions, where patients perform the exercises independently at home. In addition, we hypothesized that the differences, in terms of the above factors, between the groups in the study—intervention group and control group—were larger in the early phase of the rehabilitation but became smaller over time. The study has been registered on ClinicalTrials.gov (NCT03904030).

This study aimed to determine the effectiveness of the AlterG anti-gravity treadmill in postoperative rehabilitation after TKA. Primary outcomes were perceived pain, walking ability, and QoL. To this end, AlterG rehabilitation and traditional postoperative rehabilitation with instructions were compared.

In detail, we aimed to measure the effects of AlterG training on:

a patient’s walking ability and walking distance after TKA,a patient’s perceived QoL and functional ability after TKA,a patient’s perceived pain, andlower limb and step symmetry during gait and if it normalizes the patient’s stepping and walking.

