After the surgery, the researcher informed each patient over the phone or face-to-face about their assigned group, either the intervention or control group. After that, the researcher booked training times on the AlterG for each member of the intervention group. Patients were sent a reminder through an SMS text message on the time reserved for them to ensure that the risk of forgetting was lower. If the time did not suit the patient, the physiotherapist was informed, and a new time was reserved accordingly. The patients in the intervention group exercised 10 times on the AlterG under the supervision of a registered physiotherapist. Both groups performed traditional postoperative exercises after TKA. The follow-up period was 12 months. Exercises began in the third week after surgery. In the third and fourth weeks after TKA, patients in the intervention group exercised twice a week on the AlterG and thrice a week in the fifth and sixth weeks considering individual variations. The AlterG training was recorded 3 out of 10 times—the first, fifth, and 10th training sessions. The recording began after the patient found a suitable walking speed and lightening. On average, the length of one recording was 2 minutes. The data obtained from the AlterG training was saved to a memory stick and then transferred to an electronic folder. The patient schedule of enrollment, interventions, and assessments are shown in Table 2. The study procedure is outlined in Figure 1.

The protocol has been developed using the SPIRIT (Standard Protocol Items: Recommendations for Interventional Trials) checklist [37] (Multimedia Appendix 2).

**Table 1 table1:** Questionnaires and functional tests.

Measurement				Explanation

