### Outcome Assessment and Measurements

The primary outcomes were walking ability measured with the 6MWT, health-related QoL measured with RAND-36, and perceived pain measured with VAS. All outcomes were measured before the TKA and 4 and 12 months after the TKA. In addition to this, the patients were asked to complete the same questionnaires 6-8 weeks after the TKA. The initial measurements were performed 1-2 weeks before the TKA. Depending on the patient, it took a total of 1.5-2 hours to complete the questionnaires and execute the functional tests. The same measurements were performed 4 and 12 months after the surgery, and the time required for these was the same as in the initial measurements (1.5-2 hours). Regarding the functional tests, the test scores were not calculated within the testing situation; however, the physiotherapist noted the measurement results on the test form, which were then saved in an electronic format. The results obtained from the tests were compared throughout the study between the patient’s own results and between the intervention and control groups; no comparisons were made with the general reference values of the tests. The knee ROM and swelling, thigh muscle circumference, TUG, stair climbing test, and 6MWT were performed only once. The tests were performed twice only in the static balance test, and the best test result was recorded (the maximum time was 60 seconds).

All the measures of the study are presented in Table 1. During the AlterG training, the weight-bearing symmetry, step length, stance time symmetry, and cadence during walking were measured (Textbox 1).

AlterG measurements.

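### The gait-symmetry aim is worded as an effect of AlterG training, but gait is recorded only in the intervention arm during AlterG sessions, so no between-group effect on symmetry can be estimated

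*Protocol article*

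**What the plan says.** All references are to the protocol article.

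- **Aim.** Aims and Objectives lists what the trial will measure as effects of AlterG training. The last item is lower limb and "step symmetry during gait and if it normalizes the patient’s stepping and walking". The list follows the statement that AlterG and traditional rehabilitation were compared.
- **Hypotheses.** The same section states: "We hypothesized that AlterG training after hospitalization leads to faster rehabilitation, better walking quality, improved QoL", with traditional rehabilitation as the comparator. It adds that the differences between the groups on these factors "were larger in the early phase of the rehabilitation but became smaller over time".
- **What is recorded.** Outcome Assessment and Measurements: "During the AlterG training, the weight-bearing symmetry, step length, stance time symmetry, and cadence during walking were measured".
- **In whom.** Study Procedure: "The patients in the intervention group exercised 10 times on the AlterG under the supervision of a registered physiotherapist". Table 2 gives the control group traditional exercises only.
- **When and how.** Study Procedure: "The AlterG training was recorded 3 out of 10 times—the first, fifth, and 10th training sessions". On the conditions: "The recording began after the patient found a suitable walking speed and lightening". A recording lasted about 2 minutes on average.
- **Tests done in both arms.** Study Procedure and Table 1 give knee range of motion, swelling, thigh circumference, single-leg stance, TUG, stair climbing and 6MWT, before surgery and at 4 and 12 months. None measures symmetry, step length, stance time or cadence.

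**The concern.** An aim about the effect of a randomised treatment needs the outcome in both arms, or at least a design that separates treatment from the passage of time. For gait symmetry the article describes neither. Intervention patients are recorded only while they train on the device, in weeks when every patient in the trial is recovering from surgery.

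The question is what the trial may conclude. If the aim stands as worded, a change between the first and tenth session can be read as an effect of AlterG on gait, or as gait being normalised by it. Randomisation gives no protection to that reading. Data collection ended in 2022 and analysis is set for 2025 and 2026, so the missing data cannot now be collected. The wording of the aim can still be corrected before the results are written.

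**Working it through.** The point is structural and no calculation decides it. The check sets the aim beside the measurement schedule.

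**1. When the recordings fall.** Study Procedure gives two sessions a week in weeks 3 and 4 and three a week in weeks 5 and 6:

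2 × 2 + 2 × 3 = 10 sessions, which agrees with the stated 10.

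Sessions 1 to 4 fall in weeks 3 and 4, sessions 5 to 7 in week 5, and sessions 8 to 10 in week 6. The recorded sessions (1, 5 and 10) are therefore nominally in weeks 3, 5 and 6. The article allows for individual variation, so the window is approximate.

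**2. How many recordings exist.** With 31 patients per arm:

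| Time | Intervention arm | Control arm |
|---|---|---|
| Before surgery | none described | none described |
| About weeks 3 to 6 | at most 31 × 3 = 93 | 0 |
| 4 months | none described | none described |
| 12 months | none described | none described |

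**3. What can be estimated between groups.** The contrast at time t is mean symmetry (AlterG, t) minus mean symmetry (control, t). The second term is missing at every t, so the contrast cannot be formed. For symmetry, the hypothesis that group differences start large and shrink needs this contrast at two or more times, so it cannot be examined either.

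**4. What can be estimated within the arm.** The available quantity is the change from session 1 to session 10. Schematically:

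observed change = training effect + natural recovery + treadmill familiarisation + change due to speed and unloading.

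There is one observed quantity and four components. Session 1 is not a preoperative baseline, because training starts in the third week after surgery. No fixed test speed or unloading is described, so the conditions can differ between a patient's own recordings.

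**5. Whether the recordings speak to normalisation.** They are taken with body weight lightened, which the Introduction says makes walking less painful than land-based training. They describe supported treadmill gait. No unsupported gait recording is described that could show whether ordinary walking became more symmetrical.

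**The case against.** Several counter-arguments deserve weight.

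- **Walking quality is undefined.** A reader might infer that the walking-quality hypothesis as a whole has no randomised comparison. The document does not support that. If the term means walking capacity, 6MWT, TUG and stair climbing give randomised comparisons at 4 and 12 months. This objection stands: for that hypothesis the fault is an undefined term. It does not rescue the symmetry aim, because those tests yield distances or times.
- **This is not a primary question.** A reader might treat better walking quality as the main hypothesis. The article does not label it so; it is one item in a list. The primary outcomes are 6MWT, RAND-36 and VAS, the sample size rests on the 6MWT, and Expected Findings names walking ability, quality of life and pain. This stands and limits the weight of the point.
- **No misreporting is planned.** A reader might infer that any change over sessions will be presented as an AlterG effect. No section commits to that analysis, and Outcome Assessment and Measurements provides for comparison with the patient's own results, so a descriptive reading is open. The conclusions claim nothing about symmetry or normalisation and need no change. What remains is that the aim itself speaks of effects and normalising.
- **An analysis plan could settle it.** It could settle how the recordings are summarised. It could not supply control-arm gait data.
- **Figure 1 is not shown.** The text and Table 2 nevertheless assign AlterG to the intervention arm only.

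**Conclusion.** The symmetry aim is wrong as written. On the schedule described, there are at most 93 gait recordings in the intervention arm and none in the control arm, with no preoperative, 4-month or 12-month value in either. No between-group effect on symmetry, step length, stance time or cadence can be estimated, and the within-arm change cannot be attributed to AlterG.

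This rests on two readings: that AlterG sessions were confined to the intervention group, and that the text and tables list every gait measurement made. Both follow from Study Procedure, Outcome Assessment and Measurements, and Tables 1 and 2. The document does not show how far speed or unloading actually changed between sessions, or in which direction that would move symmetry. The conclusion needs only that they were not fixed.

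The conclusion does not extend to walking capacity, the three primary outcomes or the sample size.

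**What to change.** 1. Restate the symmetry aim as a descriptive objective within the intervention arm: change in treadmill gait parameters over sessions 1, 5 and 10. State that no claim will be made that AlterG caused the change or normalised gait.
2. Report walking speed and percentage body weight at each recording, if these were saved; the article does not say. Any model adjusting for them should be a sensitivity analysis only. Tolerated speed and unloading may themselves reflect recovery, so adjustment changes the quantity being estimated.
3. Keep the walking-quality hypothesis on record, since deleting it after data collection would be less transparent. Either tie it to a measure taken in both arms (6MWT, TUG or stair climbing), or state that gait quality was not measured in both arms and the hypothesis cannot be tested. If it is tied to one of these tests, the earliest postoperative comparison is at 4 months.

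The cost is some rewording, a short descriptive table and possibly one sensitivity model. One intended effect claim is given up. No new data are needed and no primary analysis changes.

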## Methods

### Participant Selection and Sampling Strategy

Participants for this RCT study were recruited from two hospitals in the capital region of Finland: Orton Orthopaedic Hospital and Peijas Hospital, both of which are part of the HUS Helsinki University Hospital. Patients with grades 3 and 4 primary knee osteoarthritis and with a scheduled unilateral TKA were included in the study. Those with rheumatoid arthritis, who have undergone hip or knee arthroplasties within the last year, or with a BMI >40 kg/m^2^ were excluded. All eligible patients who came for a knee arthroplasty surgery at Orton Orthopaedic Hospital between 2018 and 2021 and at Peijas Hospital between 2020 and 2021 were asked to participate in the study. The patients were recruited through a nurse’s preoperative visit or a phone call made to the patients attending the surgery. The nurse then checked whether they met the inclusion and exclusion criteria; those who met the criteria were provided with written information regarding the study. The included patients were asked to provide signed consent forms (Multimedia Appendix 1), which they forwarded to the research assistant. When the patient had consented to participate in the trial, the randomization envelope was opened after the surgery. However, due to the nature of the intervention under study (rehabilitation intervention), it was not possible to blind the patients. The patients were randomly allocated either to the treatment group or the control group using a random number generator (StatTrek) by an expert who did not execute the study in practice. All the patients had free access to the available health care services during the study. Overall, 62 patients (31 in each group) were recruited for the study.

### Study Procedure

Patients in both groups underwent initial measurements 1-2 weeks before the surgery, which included questionnaires and functional tests performed by a physiotherapist. All the measurements were taken at Orton Orthopaedic Hospital. First, the patients were asked to complete the questionnaires, and functional tests were then performed. The questionnaires used were a visual analogue scale (measures perceived pain) [20], painDETECT [21], Tampa Scale of Kinesiophobia [22], RAND 36-item Health Survey 1.0 (RAND-36) [23], Oxford Knee Score [24,25], Western Ontario and McMaster Universities Osteoarthritis Index [26], Beck Depression Inventory [27], and State-Trait Anxiety Inventory [28] (Table 1). Functional tests performed were knee range of motion (ROM) [29], knee swelling [30], thigh circumference [31], single-leg stance test [32], Timed Up and Go test (TUG) [33,34], stair climbing test [35], and 6-minute walk test (6MWT) [36] (Table 1).

Patients were asked to complete the same questionnaires 6-8 weeks after surgery. The same questionnaires and functional tests were administered in the same order 4 and 12 months after the surgery at Orton Orthopaedic Hospital. This data can help obtain information regarding short-term (4 months) and long-term (12 months) changes. Then, 6 months after the surgery, the patients were sent a 6-month questionnaire regarding possible rehabilitation sessions, use of medication, and possible complications after TKA. The purpose of this questionnaire was to obtain information regarding their use of health care services and how their rehabilitation and recovery from the surgery have progressed.

After the surgery, the researcher informed each patient over the phone or face-to-face about their assigned group, either the intervention or control group. After that, the researcher booked training times on the AlterG for each member of the intervention group. Patients were sent a reminder through an SMS text message on the time reserved for them to ensure that the risk of forgetting was lower. If the time did not suit the patient, the physiotherapist was informed, and a new time was reserved accordingly. The patients in the intervention group exercised 10 times on the AlterG under the supervision of a registered physiotherapist. Both groups performed traditional postoperative exercises after TKA. The follow-up period was 12 months. Exercises began in the third week after surgery. In the third and fourth weeks after TKA, patients in the intervention group exercised twice a week on the AlterG and thrice a week in the fifth and sixth weeks considering individual variations. The AlterG training was recorded 3 out of 10 times—the first, fifth, and 10th training sessions. The recording began after the patient found a suitable walking speed and lightening. On average, the length of one recording was 2 minutes. The data obtained from the AlterG training was saved to a memory stick and then transferred to an electronic folder. The patient schedule of enrollment, interventions, and assessments are shown in Table 2. The study procedure is outlined in Figure 1.

The protocol has been developed using the SPIRIT (Standard Protocol Items: Recommendations for Interventional Trials) checklist [37] (Multimedia Appendix 2).

**Table 1 table1:** Questionnaires and functional tests.

Measurement				Explanation
